## **RESEARCH PROTOCOL R-1242-23**

### **IMPROVING READING COMPETENCE IN APHASIA WITH COMBINED EXERCISE AND PHONO-MOTOR TREATMENT**

#### **EXECUTIVE SUMMARY AND ADMINISTRATIVE INFORMATION**

The study will recruit participants at the Kessler Institute for Rehabilitation (KIR) and other sources as detailed in the application, where our Stroke research team has been collecting very detailed information about left-hemisphere stroke patients, including the patients' mental function, and reading ability. The left-hemisphere stroke patients who meet the following inclusion criteria will be enrolled in the study:

1. Fluent and proficient in English prior to stroke
2. Left hemisphere stroke >3 months ago
3. Age range 18-85
4. Reading deficit as established through self-report and formal testing

The participants are excluded from the study if they have any other neurological disorders, if they have contraindications to MRI, or if they have a vision problem that interferes with reading, if they are unable to participate in exercise or if they are currently undergoing one-on-one speech and language therapy.

Participants will complete a total of 60 hours of reading therapy. In addition, they will engage in 20 min of aerobic exercise (cycling) or stretching prior to each treatment session along with 5-min warm up and cool down. Session duration will be capped at 2 hours, participants will complete a total of 40 sessions (30 min exercise + 90 min reading therapy per session). Participants will also undergo an MRI at baseline, on day 1 of assessments, following 30 minutes of cycling or stretching, and after treatment. Participants will be compensated \$100 for their participation.

The main goal of this study is to improve the current understanding of brain mechanisms for reading and to develop effective, evidence-based treatments for post-stroke reading deficits. A left-sided stroke often results in language and reading disabilities, where individuals encounter challenges effectively returning to work and performing basic daily tasks. This study may help to alleviate the burden of reading disabilities.

## **1. ABSTRACT**

The ability to read is an essential part of contemporary society, and its disruption because of stroke or another disorder, leads to significant reduction in independence and quality of life. Yet, much is still not known about the interplay between the information processing components of reading and their physiological underpinnings. For the last 10 years, we have been collecting neuropsychological and brain imaging data from left-hemisphere stroke survivors to study the relationship between orthography (spelling), phonology (sound), and semantics (meaning) and the brain areas that support these cognitive processes. While functional brain imaging in healthy participants allows specification of brain areas that are sufficient for reading, including patients with relevant deficits allows us to test for areas that are functionally necessary. Through this work, we have been able to identify both the impaired cognitive processes and the dysfunctional neural mechanisms which characterize individuals who experience reading deficits.

Unfortunately, many people with reading problems after stroke do not receive specific therapies, and their social and vocational participation can be adversely affected by this hidden disability. This causes not only personal losses but cost to society of their lost work and social roles. In this study we are testing the effectiveness of a novel reading intervention that was built on the bases of our previous work. This intervention combines aerobic exercise (or stretching as a control condition) with a treatment targeting impaired phonological processing, identified as the most common and persisting problem among individuals with reading deficits. Regular aerobic exercise increases brain circulation and has a beneficial effect on cardiovascular function. We propose that when it is combined with a targeted reading treatment, it will promote the acquisition, retention, and generalization of skills learned in therapy, as a result of improved oxygen and nutrient supply to the brain.

## **2. OBJECTIVES OF THE STUDY**

This study has 3 objectives:

1. To determine if the proposed intervention will improve language outcomes.
2. To examine the immediate impact of aerobic exercise on cerebral circulation
3. To examine the neural mechanisms of sustained change in reading outcomes following the proposed intervention.

To address Objective 1, we will randomize 100 chronic (>3 months post-stroke) left hemisphere stroke participants to either the aerobic exercise (AET) or the stretching condition. The AET condition will complete 20 minutes of moderate intensity aerobic exercise in the form of stationary bike cycling prior to a 1.5-hour targeted reading treatment session using phono-motor therapy (PMT) (Kendall et al., 2019). The control condition will complete 20 minutes of light

stretching before each PMT session. Both conditions will also have a 5-min warm up and cold down. All participants will complete 40, 2-hour intervention sessions administered 3-5 times per week for 8-10 weeks. We will measure reading competence as the primary outcome, and naming, auditory comprehension, and spontaneous speech as secondary language outcomes using standardized and experimental tasks administered before and after the full course of treatment. We expect a condition by time interaction, such that the AET condition will improve more than the stretching condition from baseline to end of treatment.

To address Objective 2, we will ask participants to undergo 2 MRI scans, one at baseline and one following the first AET or stretching session. The scans will assess regional and whole brain cerebral blood flow and functional connectivity to determine the immediate impact of aerobic exercise vs. stretching on neural and vascular processes. A greater increase in cerebral blood flow is expected after aerobic exercise than stretching.

To address Objective 3, we will ask participants to complete language testing and a 3rd MRI scan after completing the intervention. We expect greater increases in cerebral blood flow, brain connectivity, and task-related activation in the AET condition compared to the stretching condition. These increases are expected to be most evident in areas supporting phonology and orthography-to-phonology mapping. The increased cerebral circulation and brain activity are expected to predict reading and other language outcome gains.

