- The research staff will follow rigorous ethical protocols established at Kessler Foundation Stroke Laboratory for the protection of patients' rights and **confidentiality**. The research materials, consisting of MRI images, behavioral and questionnaire data, will be securely stored on password-protected computers in locked laboratory space. Each data file will be numbered and will have no information about the identity of the patient. The written informed consents will be kept in a locked cabinet. Only the research staff listed on the application will have access to the file identifying each patient's numeric code. The file will be kept in a secure location for the purpose of sharing the results of participant's own performance upon his/her request. After data collection is complete, the data will be available to the PIs, Co-I, and SC for review. Descriptive and inferential

statistics generated from the data will be used for further research and scientific dissemination.

- The PIs will ensure that patients are informed about the outcome of the study, as well as about their own performance, upon their request. Each patient undergoing neuroimaging will be provided with a screenshot picture of his or her brain and a full electronic copy will be provided upon request. Participants will complete 3 MRI scans (before treatment, after a single AET session, and after treatment). They will receive 60 hours of reading treatment. In addition, they will complete 20 minutes of moderate intensity cycling (prescribed individually based on heart rate) or light stretching prior to each reading treatment session. To cap treatment session duration at 2 hours, we will administer this treatment in 40 sessions. They will be paid \$100 for their participation, with payment prorated (\$50 for completing behavioral and physical assessments and 2 MRI scans; \$50 for completing assessments, therapy, and the final MRI scan).
- Patients who indicate research interest and meet the inclusion criteria will be asked to provide a written informed consent prior to any behavioral testing or MRI scanning. A copy of the informed consent is attached.

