- They will undergo 3 MRIs, including structural, perfusion, and functional sequences. Each scan will last approximately 50 minutes. The results of the scans will be used to determine the size and location of the stroke lesion, and the impact of treatment on cerebral blood flow and function. Participants will undergo 40 sessions of treatments (2 hours each). The treatment will start with 20 minutes of aerobic exercise (cycling) or stretching preceded and followed by 5 minutes of warm up and cool down. Participants' heart rate will be monitored continuously, and those undergoing aerobic exercise will be asked to exercise at a heart rate equal to 60-70% of their individual maximal heart rate (i.e., moderate intensity). Aerobic exercise will be supervised by a senior scientist with physical therapy and exercise research expertise ([name]). The exercise will be followed by 1,5 hours of reading therapy (Phono-motor treatment) (Kendall et al., 2019). The treatment fidelity will be monitored by the co-I, [name], who will review randomly selected treatment session videos at a rate of ~1 video/week/participant.
- Some participants may not complete all sessions according to the proposed schedule due to unforeseen circumstances (such as participant or staff illness, transportation problems, etc.) or because of holidays or other commitments. Efforts will be made to reschedule missed sessions as close to the original proposed dates as possible. The total length of the intervention period may also be extended if needed to provide time to reschedule missed sessions.
- In addition to assessing the rate of perceived exertion during each 5-minute exercise interval, we will ask participants to rate their enjoyment, willingness to continue to engage in the exercise program, and difficulty adhering to the program at the end of each

exercise session. We will also prompt participants for free form comments about their experience in the program.

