## C. Analysis

All variables will be examined for outliers and appropriate strategies will be instituted if problems are identified. AET+PMT and Stretching+PMT will be compared on demographic and baseline variables (including baseline hypoperfusion) using two-sample t tests, Chi-square, or

equivalent non-parametric tests, as appropriate. Effect sizes (ES) will be calculated for all primary and secondary analyses. As recommended by Hahn (Hahn, 2012) for active control trials, we will conduct both intent-to-treat and per-protocol analyses and conclude AET+PMT superiority on the primary outcomes if both analyses support it. Per-protocol analyses will be conducted in those completing follow-up testing and in those who demonstrated good adherence and compliance. We will define adherence/compliance as completing at least 34 of the 40 possible treatment sessions as prescribed. This approximates the 85% adherence guideline for internal validity for RCTs based on the Physiotherapy Evidence Database (PEDro) scale. (Sherrington et al., 2000) Should attrition exceed expectations, we will use two-sample t-tests, Chi-square tests, or non-parametric equivalents to compare all baseline variables between subjects who remain in the study and those who drop out. Further specific analyses are described below.

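### Outcome testing is timed only to completing treatment, with no stated provision for participants who stop early, so the required intent-to-treat analysis risks becoming a completers' analysis

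*Protocol*

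**What the plan says.** **Timing of the outcome.** Section 2 (Objective 1) has the language outcomes measured with "standardized and experimental tasks administered before and after the full course of treatment". For Objective 3, "we will ask participants to complete language testing and a 3rd MRI scan after completing the intervention". Section 5.B gives the order as baseline assessments, treatment, outcome assessment. The protocol gives no outcome week or window.

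**Course length.** Section 2 states: "All participants will complete 40, 2-hour intervention sessions administered 3-5 times per week for 8-10 weeks". Section 5.B is less certain: "Some participants may not complete all sessions according to the proposed schedule due to unforeseen circumstances". It asks that missed sessions be made up near their original dates and adds: "The total length of the intervention period may also be extended if needed to provide time to reschedule missed sessions". No maximum is given.

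**Payment.** Section 5.A splits the $100 into two halves. The second $50 is "for completing assessments, therapy, and the final MRI scan".

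**Analysis.** In Section 5.C, "we will conduct both intent-to-treat and per-protocol analyses", and superiority is concluded only if both support it. The per-protocol set is described by completion of follow-up testing and by adherence: "We will define adherence/compliance as completing at least 34 of the 40 possible treatment sessions as prescribed". The primary comparison is a 2x2 repeated-measures design, condition by session, with one baseline and one outcome value. If attrition is higher than expected, the stated response is to compare the baseline data of those who stay and those who leave. No expected attrition rate is given.

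**The concern.** An intent-to-treat analysis needs outcome data sought from everyone randomised, including those who stop treatment. Here the outcome visit is described only as what follows a finished course. Staff following that text have no instruction to bring back a participant who stops halfway, no date on which to do it, and no stated payment for that visit alone.

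If early stoppers go untested, the intent-to-treat set shrinks towards the people who finished, which is close to the per-protocol set. Requiring both analyses to agree would then add little protection. If stopping also depends on arm and is related to reading gain, the primary interaction is biased. Differential stopping is plausible from the protocol itself: Section 5.A lists musculoskeletal injury, irregular heart rhythm and shortness of breath as risks of moderate exercise, which only the cycling arm performs.

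This is a data-collection rule. A later SAP can say how missing outcomes are handled, but it cannot recover outcomes that were never collected.

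**Working it through.** **1. The protocol's own figures.** 34/40 = 0.85, which matches the 85% adherence guideline it cites. 40 sessions x 1.5 h = 60 h, which matches the stated therapy dose. The sample of 100 cannot be reproduced because the protocol gives no effect size, SD, power or dropout.

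**2. What one missing outcome costs.** With two time points, the condition-by-session interaction is the difference between arms in mean change:

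(post − baseline in cycling) − (post − baseline in stretching).

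A participant with a baseline value only has no change score. A likelihood-based model would keep the baseline value, but that value carries almost no information on the post-treatment contrast.

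**3. Bias if stoppers are untested.** Let p be the proportion stopping in an arm and g the amount, in SD of change, by which stoppers gain less than completers. The mean over all randomised participants is the completers' mean − p·g, so analysing completers overstates that arm by p·g. With the same g in both arms:

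net bias = (p_cycling − p_stretching) × g.

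Neither p nor g is in the protocol. With g = 0.5 assumed:

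| Stopping, cycling v stretching (assumed) | Net bias, SD (positive favours cycling) |
|---|---|
| equal | 0 |
| 15% v 10% | 0.05 x 0.5 = 0.025 |
| 20% v 5% | 0.15 x 0.5 = 0.075 |
| 30% v 5% | 0.25 x 0.5 = 0.125 |
| 5% v 20% | −0.15 x 0.5 = −0.075 |

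**4. Scale.** Assume 1:1 allocation, two-sided 5% and 80% power, with SD of change = 1. The detectable difference is (1.96 + 0.84) x sqrt(2/n), where n is the number measured per arm.

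| Measured in total | Detectable difference, SD | Power at 0.56 SD |
|---|---|---|
| 100 | 0.56 | 80% |
| 90 | 0.59 | 76% |
| 80 | 0.63 | 71% |
| 70 | 0.67 | 65% |

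A bias of 0.075 SD is about 13% of 0.56 (0.075/0.56); 0.125 SD is about 22%.

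**5. When the course ends.** 40 sessions take 40/5 = 8.0 weeks at five per week, 40/4 = 10.0 at four and 40/3 = 13.3 at three. Three per week therefore does not fit the stated 8-10 weeks; that pace gives 24 to 30 sessions in that time, below the 34-session adherence threshold. A visit tied to course completion can fall anywhere from week 8 to beyond week 13 before any extension.

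**The case against.** The strongest reply is that the protocol is silent rather than wrong. A reader might infer that early stoppers have no outcome measurement and that the intent-to-treat analysis cannot be delivered. The documents do not support that: nothing forbids testing early stoppers, and other phrases, such as end of treatment, do not require a fortieth session.

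A reader might also infer that participants with 34 to 39 sessions are adherent yet never reach the outcome visit. The adherence rule points the other way. It places them in an analysis that needs outcome data, and it names follow-up testing separately from adherence, so testing without all 40 sessions is evidently expected. The wording of Section 2 and the 34-of-40 rule fit badly together, but the rule is evidence against a strict trigger.

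Four further replies deserve weight:

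- The Participant Status Form in the DSMB section lists one-month and three-month follow-ups, so the post-treatment visit may not be the only later contact. The body of the protocol does not describe those visits. The form places the immediate follow-up after treatment completion and has one field for not completing the study, so it does not close the gap.
- Extension of the treatment period is tempered by the instruction to reschedule close to the original dates, and it applies to both arms. Testing after a fixed amount of therapy is a legitimate choice for a training intervention.
- Payment is described as prorated, and whether the second half deters anyone from returning is conjecture. What stands is that no payment is stated for attending the outcome visit alone.
- The stopping rates and the 0.5 SD deficit are assumptions. Both arms share the same 90 minutes of therapy per session, so large differential stopping is not established.

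What survives is the absence of any provision to assess early stoppers in a trial whose superiority claim depends on an intent-to-treat analysis.

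**Conclusion.** The point holds as a risk to the intent-to-treat analysis. It does not show that the analysis is impossible. Outcome testing and the third MRI are tied only to completing treatment, no provision is stated for participants who stop early, and the second payment is linked to therapy as well as assessments. With a single post-treatment value, untested stoppers drop out of the primary comparison, and the intent-to-treat result moves towards a completers' result.

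The size cannot be fixed from the protocol. Bias is zero if stopping and the stoppers' deficit are equal across arms, about 0.075 SD towards cycling at 20% v 5% with an assumed 0.5 SD deficit, and reversed in sign if the rates are reversed. The loss of precision under the assumptions above is from 80% to about 71% power if 80 of 100 are measured. The spread in outcome timing could also differ by arm, but that effect is not quantified here.

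**What to change.** In Sections 2 and 5.B:

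- State that the outcome tests and third MRI are sought from every randomised participant regardless of the number of sessions completed. Hold the visit at the end of the participant's treatment or, for early stoppers, when their course was due to end, with the same stated window in both arms.
- Record stopping treatment separately from leaving the study, including on the Participant Status Form.

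In Section 5.A, make the assessment part of the second payment payable for attending the outcome visit whether or not therapy was completed.

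Before the window is set, the sponsor must reconcile the stated session frequency with the stated 8-10 weeks for 40 sessions. Otherwise a window built on the stated length could catch participants who are on schedule but still in mid-course.

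The cost is protocol wording, a few extra outcome visits for early stoppers and the associated payments. Participants who finish normally are still tested at the end of their treatment.

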### **3. SIGNIFICANCE OF THE STUDY**

Completing this project has the potential to transform the status quo of neurorehabilitation approaches for aphasia by advancing innovative strategies that promote plasticity and enhance stroke recovery. Combining AET with specific cognitive interventions presents a unique opportunity to dramatically increase the impact of these interventions, and ultimately improve the lives of the 2.5 million Americans living with aphasia.

### **4. REVIEW OF THE LITERATURE**

A growing number of studies suggest that stroke-related *hypoperfusion* – decreased delivery of oxygen and nutrients by the blood supply – can linger for months after stroke onset (Brumm et al., 2010; Hillis, 2007; Richardson et al., 2011; Thompson et al., 2017; Walenski et al., 2022). Hypoperfusion in the non-lesioned parts of the affected left hemisphere contributes to language and reading deficits (Boukrina et al., 2019; Cloutman et al., 2011; Thompson et al., 2017). For example, we have shown that hypoperfusion of the left neural network for reading (excluding the lesion) ~1 month after stroke predicts worse accuracy on phonological tasks in the same individuals >3 months after stroke (Boukrina et al., 2019). We also found that phonological competence, critically important for reading (Beeson et al., 2022; Crisp and Lambon Ralph, 2006; Madden et al., 2018; Rapcsak et al., 2009), remains impaired in participants with subacute and chronic left-hemisphere stroke. Thus, recovery of reading may be improved by remediating phonological processing while augmenting cerebral blood flow in the affected hemisphere. Our central hypothesis is that a single bout of aerobic exercise will increase cerebral blood flow, and

if delivered before a PMT session, will facilitate treatment-induced plasticity, ultimately leading to robust reading improvements over time. In a previous study, 6 months of moderate intensity AET was shown to increase global cerebral blood flow by 15%, with the largest effects found in the parietal lobe (Robertson et al., 2017), a brain region thought to support, among other things, phonological processing (Cattinelli et al., 2013). AET also improved cognitive function in cognitively impaired individuals (Mayer et al., 2021; Northey et al., 2018) and 15 minutes of aerobic cycling exercise improved performance on a working memory task in stroke patients.

While prior published studies point to the positive impact of AET on cognitive recovery in stroke, few studies include individuals with aphasia and most do not use adequate language testing or properly report aphasia characteristics (Mayer et al., 2021) This project will fill the apparent gap in the literature on the mechanisms and potential impact of aerobic exercise on recovery of reading in post-stroke aphasia. We posit that AET will increase cerebral blood flow and promote re-learning of language skills during an intensive PMT targeting reading, as compared to a control stretching condition.

